#### Blinding

All participants will be blinded to the treatment received. Placebos will be prepared by a pharmacist to resemble metformin PR in shape, size, and color. All caring obstetricians will be blinded to the treatment and make decisions on dosage adjustment or initiation of insulin therapy at their discretion. Glycemic control will be blindly assessed by the investigators without knowing the group to which the participants are assigned.

In case of withdrawal or termination of the study protocol, such as the occurrence of severe adverse events or noncompliance, the treatment will be unblinded. Further individualized management will be provided as appropriate. In addition, emergency unblinding will be performed if the participants need to be evaluated or treated for medical or obstetric conditions other than GDM.

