## Methods

### Study Design

The study is designed as a randomized, double-blind, placebo-controlled trial and registered at the Thai Clinical Trial Registry (TCTR20250525007). Eligible participants will be randomly assigned in a 1:1 ratio to receive either metformin PR or a placebo. Each participant will be followed up every 2 weeks for glycemic control evaluation and dosage adjustment for 6 weeks.

According to the institutional practice guidelines, every woman with GDM will receive counseling by certified diabetes educator nurses and will be scheduled for follow-up every 2 weeks for glycemic control evaluation. If the glycemic target is not achieved after 6 weeks of intensive nutritional therapy, additional pharmacological treatment will be initiated. Therefore, this study will evaluate the primary outcome of glycemic control at 6 weeks after randomization.

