If any of the conditions in the exclusion criteria are detected after enrollment, such as congenital anomalies, randomization concealment will be revealed and considered as a dropout, and these participants will not be included in the analysis. The pregnant woman will be thoroughly evaluated by the obstetrician team to provide appropriate management.

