#### Adverse Event Reporting and Harms

Any adverse events will be evaluated by self-report from the participants and by interview and clinical evaluation during each visit (every 2 weeks), starting from the day of enrollment until the end of the study (at 6 weeks after enrollment). In addition, participants will be contacted every 2 days via a telephone call, SMS, or other online platform to evaluate any adverse events. A telephone number will be given to all participants to call if there are any suspected abnormalities or any adverse events. Attending obstetricians will assess whether the events are related to the investigational drugs used for GDM. Management will be provided as appropriate by attending obstetricians, and consultation with other specialists will be made as necessary. In case of any adverse events, an additional specific follow-up schedule with related specialists will be offered until they are resolved or considered stable. Assessment of the adverse events and their response to treatment will be by telephone call, self-report, and clinical and laboratory assessment, as appropriate, according to the contexts and nature of the events. All the events will be followed up on until the conditions resolve. All the adverse events will be recorded in detail in the case record form.

In case of withdrawal or termination of the study protocol, such as severe adverse events or noncompliance, treatment will be unblinded. Further individualized management will be provided as appropriate.

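### Unblinding is ordered for any evaluation of a non-GDM condition, and on withdrawal or termination, without requiring that the allocation be needed for care, so the blind can be broken before the 6-week outcome is read

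*Protocol article*

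**What the plan says.** The Blinding section of the protocol article makes two steps depend on the blind. For treatment decisions: "All caring obstetricians will be blinded to the treatment and make decisions on dosage adjustment or initiation of insulin therapy at their discretion". For the outcome: "Glycemic control will be blindly assessed by the investigators without knowing the group to which the participants are assigned".

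The next paragraph of that section gives two rules for breaking the blind, both in mandatory wording.

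- On withdrawal or termination: "such as the occurrence of severe adverse events or noncompliance, the treatment will be unblinded". The section Adverse Event Reporting and Harms repeats this: "In case of withdrawal or termination of the study protocol, such as severe adverse events or noncompliance, treatment will be unblinded".
- On other conditions: "emergency unblinding will be performed if the participants need to be evaluated or treated for medical or obstetric conditions other than GDM".

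A third rule, in Interventions, covers exclusion criteria discovered after enrollment: "randomization concealment will be revealed and considered as a dropout, and these participants will not be included in the analysis". Those women leave the analysis, so they are not part of this point.

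On timing, Study Design states that "this study will evaluate the primary outcome of glycemic control at 6 weeks after randomization". Statistical Methods puts all analyses on an intention-to-treat basis and plans multiple imputation for missing values.

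**The concern.** The second rule is called emergency unblinding but sets no threshold of urgency or severity. Read literally, needing to be evaluated for any medical or obstetric condition other than GDM is enough, whether or not the allocation would change what is done. These are pregnant women seen every 2 weeks and contacted every 2 days about adverse events, so there are many occasions on which such a condition could come up before week 6.

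A woman unblinded in this way is still on study. Her later dose adjustments, her individualized counselling, any insulin decision and her own glucose readings could all be influenced by knowledge of the arm, and under intention to treat she counts in the comparison. At stake is the double-blind design, which the article lists among its strengths. This is a rule the article states, not a detail left to a fuller document.

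**Working it through.** **1. The rules against the blinding statements.**

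| Rule | What sets it off | Must the arm be needed for care? | Can act before week 6? | Woman still analyzed? |
|---|---|---|---|---|
| Non-GDM condition (Blinding) | Need for evaluation or treatment | Not required | Yes | Yes, with an observed outcome if she stays on study |
| Withdrawal or termination (Blinding; Adverse Event Reporting and Harms) | Leaving the protocol, for example for a severe adverse event or noncompliance | Not required | Yes | Yes under intention to treat; outcome observed or imputed |

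The first row carries most of the weight, because it reaches women who continue in the trial. In the second row some women will have no week-6 reading for knowledge of the arm to affect.

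**2. Which steps are open to influence.** Dose and insulin decisions are discretionary (Blinding). Counselling is individualized at every follow-up visit (Interventions). The primary outcome uses the share of self-monitored results within target (Outcomes), and glucometer use is by the woman's preference (GDM Diagnosis and Management). In the other direction, the target is a numeric threshold, and fasting and 2-hour glucose may be recorded at visits (Data Collection and Management).

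**3. When insulin decisions fall.** The step-up order is 750, 1000, 1500 and 2000 mg, with adjustment every 2 weeks. Starting at 750 mg, one step each at weeks 2, 4 and 6 reaches 2000 mg at week 6. Interventions defines treatment failure as inadequate control after 2000 mg, and the Abstract starts insulin if the target is not met within 6 weeks. Most insulin decisions therefore fall at or after the primary reading. Earlier insulin at the obstetrician's discretion is possible.

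**4. Illustration of size.** The documents give neither an unblinding rate nor the effect of unblinding, so both are assumptions.

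The sample size comes first. The planned rates are 95% and 70%, with 80% power, 95% confidence and 20% loss. The arcsine formula with two-sided 5% gives h = 2·asin(√0.95) − 2·asin(√0.70) = 0.708, then n = 2(1.960 + 0.842)²/0.708² = 31.3, rounded up to 32. With loss, 32/0.80 = 40 per group, which matches the plan. I take 32 analyzed per group as the base.

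True null: 82.5% in both arms, the mean of 95% and 70%. Let u be the fraction of analyzed women unblinded, and d the probability that an unblinded metformin failure is read as a success or an unblinded placebo success as a failure. Every shift then favors metformin.

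- Metformin PR: 0.825 + 0.175·u·d
- Placebo: 0.825 − 0.825·u·d
- Spurious difference: (0.175 + 0.825)·u·d = u·d

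Exact rejection probability of the two-sided 5% Pearson chi-square test:

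| u | d | Metformin PR | Placebo | Difference (points) | 32 per group | 40 per group |
|---|---|---|---|---|---|---|
| 0 | – | 82.50% | 82.50% | 0 | 5.1% | 5.2% |
| 10% | 10% | 82.68% | 81.68% | 1.0 | 5.2% | 5.3% |
| 10% | 25% | 82.94% | 80.44% | 2.5 | 5.8% | 6.1% |
| 10% | 50% | 83.38% | 78.38% | 5.0 | 8.0% | 8.9% |
| 20% | 10% | 82.85% | 80.85% | 2.0 | 5.6% | 5.8% |
| 20% | 25% | 83.38% | 78.38% | 5.0 | 8.0% | 8.9% |
| 20% | 50% | 84.25% | 74.25% | 10.0 | 16.6% | 19.7% |

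The 40-per-group column treats all randomized women as analyzed. If few women are unblinded, or knowing the arm rarely changes a reading, the error rate stays close to nominal.

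**The case against.** The strongest reply is that the article, read as a whole, does not mean to unblind for routine care. The sentence speaks of emergency unblinding. Safety Management places obstetric examination and fetal assessment within standard antenatal care at every visit. Adverse Event Reporting and Harms has obstetricians assess and manage events, and mentions unblinding only for withdrawal or termination. The outcome is a glucose threshold, which the article calls objectively measured. Much of this stands, and it rules out several stronger readings.

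- **That any noncompliance breaks the blind.** Noncompliance is an example of a reason for withdrawal or termination. Interventions answers pill counts with further encouragement, so a missed tablet is not clearly a trigger.
- **That a large share of ordinary visits would lead to unblinding.** The documents give no frequency, and their account of routine care points the other way.
- **That the planned 20% loss, 16 of 80 women, measures unblinding.** Loss is not unblinding. Women truly lost have no week-6 reading to bias, and they are not among the 32 per group who remain. The 20% used above is an assumed rate among analyzed women.
- **That discretionary insulin drives the primary result.** The step-up schedule puts most such decisions at or after week 6, so they bear mainly on the insulin rate, a secondary outcome.
- **That the outcome assessor is told the arm.** Nothing says so. Who is told and how cases are logged are details an article may leave to the full protocol.

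Unblinding for a severe adverse event is ordinary and is not questioned here. What the reply does not remove is the wording itself: the rule is mandatory, evaluation alone satisfies it, and need for the allocation is not a condition.

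**Conclusion.** The concern holds as a conflict within the protocol article. It claims blinded treatment decisions and blinded assessment up to week 6, yet its own unblinding rules, followed as written, can remove the blind earlier for women who stay on study and in the analysis. The claim is weakened mainly for dose adjustment, counselling, insulin and self-monitored readings, and less for the thresholded primary outcome.

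The size of any bias cannot be derived from the documents. The range of 5.2% to 16.6% at 32 per group rests on assumed unblinding of 10% to 20%, an assumed shift of 10% to 50%, and every shift favoring metformin. It shows sensitivity and is not a forecast. A reader might infer that the primary result will be biased by a known amount; the documents do not support that.

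**What to change.** Reconcile the triggers in Blinding and in Adverse Event Reporting and Harms with the blinding statements.

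1. Tie unblinding to the treating clinician's own judgement that the allocation is needed for the woman's care, and not to evaluation of another condition, or noncompliance-related withdrawal, in itself. What counts as needed stays with the clinician.
2. State that whoever assesses glycemic control remains blinded after any unblinding.
3. State that the week-6 outcome is still collected and analyzed for unblinded women.
4. Log each unblinding and report the number by arm, with timing relative to week 6.

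The cost is protocol wording and a log. The clinician stays free to unblind whenever care requires it. The article reports 24 of 80 women as having agreed to take part; on that count 80 − 24 = 56 would still be recruited under clearer rules.

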### Data Collection and Management

Data will be collected at enrollment and at every visit. Data will be entered into the electronic case record form, including baseline and obstetric characteristics, such as age, parity, and prepregnancy BMI. GDM diagnosis and management data, such as gestational age at diagnosis, results of the 50-g glucose challenge test and 100-g oral glucose tolerance test, and glycated hemoglobin, will be collected. Glycemic control data, including FPG and 2-hour PPG at every visit, or percentage of abnormal SMBG test results, will also be noted. Furthermore, the time to achieve the glycemic target will be evaluated, as will side effects, such as bloating, nausea, and vomiting.

Data at every time point will be checked for completeness and entered into the electronic case record form using an electronic data capture system. Data range and values will be rechecked by another research assistant. Incomplete and invalid data will be rechecked with those in the case record form or medical record. An audit trail will be used to track and identify all actions performed on the data, ensuring data integrity.

### Statistical Methods

Descriptive statistics, including number, percentage, mean, and SD, will be used to describe variables as appropriate. Comparisons of variables between groups will be made using the 2-tailed Student *t* test for continuous variables, such as age, BMI, and gestational age, or the chi-square test for categorical variables, such as parity and GDM risk factors. Comparison of rates of achievement of optimal glycemic control between groups will be performed using the chi-square test. Relative risks and 95% CIs will be evaluated. Time to achieve glycemic control will be compared between groups, using the Student *t* test or Mann-Whitney *U* test, depending on the distribution of the variables. Kaplan Meier curves will be used to estimate the survival curve of time to achieve glycemic control after treatment, and the log-rank test will be used to compare the survival curves between treatment and control groups. Rates of insulin therapy and side effects will be compared using appropriate statistical tests. Missing values will be handled using multiple imputation methods, as appropriate. Subgroup analysis by BMI categories, parity, or GDM risks will be performed as appropriate. All analyses will be performed on an intention-to-treat basis. A *P* value of <.05 is considered to indicate statistical significance.

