### Outcomes

The primary outcome of this study is the rate of achievement of optimal glycemic control within 6 weeks, which is defined as FPG <95 mg/dL or 2-hour PPG <120 mg/dL in >80% of total SMBG test results.

The secondary outcomes include time to achievement of optimal glycemic control, rate of insulin therapy, and rate of side effects. Treatment failure is defined as inadequate glycemic control after 2000 mg of metformin PR. In this situation, insulin therapy is initiated. Side effects will be evaluated by interviewing the participants at each visit and by additional contact via a telephone call, SMS, or other online platforms.

The participant timeline is displayed in Figure 1.

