**Figure 1 figure1:**
[figure not shown]
Study flow diagram.

The rate of achievement of glycemic target within 6 weeks among women with GDM receiving metformin PR and placebo is estimated to be 95% and 70%, respectively, from a pilot data collection. At 95% confidence and 80% power, at least 40 women with GDM are required in each group, estimating a loss of 20% of the participants.

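### Time to glycemic control gets two between-group comparisons with neither named as governing, and the t test or Mann-Whitney comparison is unsuited to women who do not reach control by 6 weeks

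*Protocol article*

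**What the plan says.** Time to control is a secondary outcome, listed first in the Outcomes section: "The secondary outcomes include time to achievement of optimal glycemic control, rate of insulin therapy, and rate of side effects". The Statistical Methods section gives it two between-group comparisons in consecutive sentences:

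- The first says "Time to achieve glycemic control will be compared between groups" by a t test or a Mann-Whitney test, with the choice left to the shape of the data.
- The second is a survival analysis: "Kaplan Meier curves will be used to estimate the survival curve of time to achieve glycemic control after treatment". For the test between arms it adds that "the log-rank test will be used to compare the survival curves between treatment and control groups".

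The section does not say which comparison decides the outcome, or what time a woman without control at 6 weeks receives in the first one. Two general statements follow: "Missing values will be handled using multiple imputation methods, as appropriate" and "All analyses will be performed on an intention-to-treat basis".

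The Study Design section sets visits every 2 weeks for 6 weeks. The sample size paragraph below Figure 1 says that the rate of control within 6 weeks "is estimated to be 95% and 70%, respectively, from a pilot data collection" for metformin PR and placebo.

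**The concern.** Time to control is censored at 6 weeks, and the expected censoring differs sixfold between the arms (30% against 5%). A t test needs a number for every woman, so something must be done with those who have none. Each route has a defect:

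- Dropping them compares subsets selected by an outcome that arises after randomization, and departs from the stated intention-to-treat basis.
- Giving them 6 weeks scores failure the same as success at week 6.
- Imputing a time invents a date for an event that was not observed.
- Ranking them worst is sound for Mann-Whitney but unavailable to the t test, and the section does not state it.

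With a second test on the same outcome and no order between them, two answers may be available once the data are in. The stakes are more than formal. The Introduction puts time to control in the hypothesis, and the Discussion presents it as something no previous study of metformin has reported and as a guide to follow-up schedules.

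**Working it through.** **Inputs.** From the protocol: control within 6 weeks 95% v 70%; 40 women per arm; 20% loss; visits at 2-week intervals to week 6. Assumed: two-sided 5% level, control first seen at week 2, 4 or 6, and the timing patterns below.

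**The plan's own figure.** The protocol gives no figure for time to control. Its sample size for the primary outcome can be reproduced with the arcsine formula: n = 2(1.96 + 0.84)² / h², with h = 2·arcsin√0.95 − 2·arcsin√0.70. This gives 31.3, rounded up to 32, and 32/(1 − 0.20) = 40. I therefore use 32 evaluable women per arm.

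**Women without a time.**

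| | Metformin PR | Placebo |
|---|---|---|
| Of 32 | 0.05 × 32 = 1.6 | 0.30 × 32 = 9.6 |
| Of 40 | 2 | 12 |

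An achievers-only comparison would use about 30 v 22 of the 32 women per arm.

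**Timing patterns.** All end at 95% v 70%.

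- (a) Equal timing among achievers: 40/35/25% of them at weeks 2/4/6 in both arms. Mean among achievers is 0.40×2 + 0.35×4 + 0.25×6 = 3.7 weeks in each.
- (b) Constant hazard per visit, q = 1 − (1 − p)^(1/3): 0.63 v 0.33. Mean among achievers is 2.85 v 3.48 weeks.
- (c) Late extra responders: placebo achievers split 50/30/20, so 35%, 21% and 14% of the arm. Metformin PR is the same plus 25% at week 6, so 35%, 21% and 39%. Metformin PR is never behind at any visit.

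For (c), by hand:

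- Achievers only, metformin PR: (0.35×2 + 0.21×4 + 0.39×6)/0.95 = 3.88/0.95 = 4.08 weeks.
- Achievers only, placebo: (0.35×2 + 0.21×4 + 0.14×6)/0.70 = 2.38/0.70 = 3.40 weeks. Placebo looks faster.
- Non-achievers given 6 weeks: 3.88 + 0.05×6 = 4.18 v 2.38 + 0.30×6 = 4.18. The benefit vanishes from the mean.

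**Rejection rates by simulation, 32 per arm.**

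| Pattern | t test, achievers only | t test, non-achievers given 6 weeks | Log-rank, all women |
|---|---|---|---|
| (a) | 5% | 28% | 64% |
| (b) | 34% | 84% | 90% |
| (c) | 28%, essentially all favoring placebo | 5%, split between directions | 31%, essentially all favoring metformin PR |

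Runs of 2,500 to 5,000 trials per pattern moved no figure by more than about 3 percentage points. Mann-Whitney on achievers behaves like the t test on achievers. With non-achievers ranked worst, it favors metformin PR in 85% of trials in (b) and 12% in (c), and placebo in well under 1%.

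**Cost of not naming a governing test.** The achievers-only t test and the log-rank test disagree on significance in about 63%, 58% and 53% of trials under (a), (b) and (c).

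**The case against.** The strongest reply is that the sound analysis is already planned: the log-rank test uses all women and handles those without control. The remaining fault would then be a redundant second test on a secondary outcome of a self-described pilot, and the handling of non-achievers could be left to the analysis plan. The first part stands: time to control is not compared by t test or Mann-Whitney alone. The second does not excuse the text, because the unsuitable test is stated as the comparison, not left open.

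A reader might infer that the t test or Mann-Whitney will use only women who achieved control, and so will favor the wrong arm. The protocol does not support this. It never restricts that comparison to achievers, and it states intention to treat for all analyses. The reversal needs both achievers-only handling and late extra responders:

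- Under a constant hazard it does not occur.
- With the 25% extra responders split between weeks 4 and 6, placebo is favored in about 15% of trials.
- With them spread evenly over the three visits, placebo is favored in about 5%.
- With non-achievers given 6 weeks or ranked worst, there is no material reversal.

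It is also fair that the protocol does not define the unit of time to control. The 2, 4 and 6 week grid is inferred from the visit schedule.

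**Conclusion.** The point holds as a badly chosen stated method together with an unresolved duplication. One of the two planned comparisons cannot properly accommodate an expected 5% of metformin PR and 30% of placebo women, and nothing says that the other governs.

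Loss of power is the more general consequence. In all three patterns the t test detects a benefit of metformin PR less often than log-rank does, whether non-achievers are dropped or given 6 weeks. The loss is small in one case, 84% v 90% under a constant hazard with 6 weeks assigned. A result favoring placebo is a conditional risk, not a prediction.

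The censoring fractions rest on the protocol's own rates. The rejection rates rest on the assumed timing and on 32 evaluable women per arm. The log-rank test is itself not strong when the benefit comes late (31%), so naming it removes the distortion but does not guarantee power for this outcome. The primary outcome and the 40 per arm are not touched.

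**What to change.** Delete the sentence that assigns a t test or Mann-Whitney test to time to control. Name the log-rank test, already planned, as the only between-group test for this outcome, on all randomized women. State two analysis rules:

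- A woman who has not achieved control is censored at week 6.
- A woman started on insulin before achieving control stays in the analysis as not achieved to week 6. This concerns the analysis only, not when insulin is given.

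Report Kaplan-Meier cumulative proportions with control at weeks 2, 4 and 6 by arm. A discrete-time model for the tied visit times is optional and not needed to correct the fault.

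The cost is wording only, with no new data, visits or participants. The Results section expects recruitment to run to September 2026, so the change can be recorded before unblinding.
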